### Sample size {14}

Numbers of patients in the four study arms have been calculated to attain 80% statistical power at two-sided 5% alpha level [90–92], with an expected dropout rate of 27%. The sample size is based on the two-sample *t*-test (R package “pwr”, functions “pwr.t.test” and “pwr.t2n.test”).

The number of subjects to be included has been determined based on the primary endpoint, namely the number of ovulations over 6 months (from month 9 to month 15). This design will cover to detect a 0.922 mean difference between placebo and SPIOMET arms. The standard deviation of 1.96 is based on previous evidence [14, 15]. The same difference and standard deviation are considered for potentially subsequent hierarchical comparisons (see the section “Trial design {8}”).

A sample size of 364 AYAs with PCOS [at least 180 of whom will be aged < 18.0 years at study start] is required using a 1:1:1:1 allocation ratio for placebo, PIO, SPIO and SPIOMET. The number of participants to be recruited is thus 91 per treatment arm (Table 5). Assuming a 27% dropout rate, approximately 266 patients (~ 66 or 67 per treatment arm) are estimated to complete the study.

**Table 5 Tab5:** Sample size and minimum detectable differences among comparison groups

Allocation ratio	1:1:1:1	

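### The stated 80% power for placebo vs SPIOMET does not follow from the plan's own inputs: the 66 or 67 expected completers per arm give about 77%

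*Protocol article*

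**What the plan says.** All the inputs are in the protocol article, section Sample size {14}.

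- Target: "Numbers of patients in the four study arms have been calculated to attain 80% statistical power at two-sided 5% alpha level", with an expected dropout of 27%.
- Method: "The sample size is based on the two-sample *t*-test", using the R package pwr.
- Effect: "This design will cover to detect a 0.922 mean difference between placebo and SPIOMET arms". The endpoint is the number of ovulations from month 9 to month 15.
- Variability: "The standard deviation of 1.96 is based on previous evidence".
- Size: 91 per arm, 364 in total, which "is required using a 1:1:1:1 allocation ratio for placebo, PIO, SPIO and SPIOMET".
- Expected completers: "Assuming a 27% dropout rate, approximately 266 patients", given as 66 or 67 per arm.

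Table 5 repeats 80% for placebo vs SPIOMET and lists 64%, 51%, 41% and 33% for the four later steps of the fixed sequence.

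Two other sections bear on the point. Section {20c} puts all randomised patients in the main analysis and imputes incomplete primary data. Section {11b} treats stopping the study medication as dropout, with no further study procedures.

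**The concern.** A sample size that allows for dropout should give the target power in the patients who remain. Here the section names both the target (80%) and the number who remain (66 or 67 per arm), and the second does not produce the first.

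Placebo vs SPIOMET is the first test in the fixed sequence, and no later comparison can be claimed unless it succeeds. Its power is the figure that justifies 364 patients, at least 180 of them under 18. The later rows of Table 5 are built from the same 80%, so an error there carries down the column.

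**Working it through.** **Inputs** (all from Sample size {14}): difference 0.922, SD 1.96, two-sided alpha 0.05, target power 0.80, dropout 0.27, 91 randomised per arm.

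**1. Completers.** 364 × 0.73 = 265.7, so 266. 91 × 0.73 = 66.4 per arm. The article's 266 and its 66 or 67 per arm reproduce.

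**2. Standardised difference.** d = 0.922 / 1.96 = 0.4704.

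**3. Patients needed for 80% power.** Normal approximation: n = 2 × (1.960 + 0.842)² / 0.4704² = 70.9, so 71 per arm. Exact two-sample t-test (noncentral t, the calculation in pwr.t.test): n = 71.9, so 72 per arm.

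**4. Power at the relevant sizes.** The noncentrality is d × √(n/2), with 2n − 2 degrees of freedom.

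| Evaluable per arm | Noncentrality | Power |
|---|---|---|
| 66 | 0.4704 × √33 = 2.70 | 76.5% |
| 66 vs 67 | – | 76.8% |
| 67 | 0.4704 × √33.5 = 2.72 | 77.1% |
| 72 | 0.4704 × √36 = 2.82 | 80.0% |
| 91 (no loss) | 0.4704 × √45.5 = 3.17 | 88.4% |

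Other conventions do not recover 80% at 66 or 67 per arm. The normal approximation gives 77.1% to 77.7%, the error degrees of freedom of a four-arm ANOVA give 76.8% to 77.4%, and a one-sided 5% test gives 85% to 86%. Rounding of the SD is not the explanation either, since 80% at 66 or 67 per arm would need an SD of about 1.88 to 1.89.

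**5. Detectable difference.** At 80% power, 66 to 67 per arm detect 0.963 to 0.956, that is about 0.96.

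**6. Where 91 may come from.** Dividing by the retained fraction, 72 / 0.73 = 98.6, so 99 per arm and 396 in total. Multiplying, 71.9 × 1.27 = 91.3 (or 71 × 1.27 = 90.2, rounded up to 91). Of the routes tried, only multiplication by 1.27 lands on 91.

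**7. Loss that 91 per arm can absorb.** 1 − 72/91 = 0.209, so about 21%, not 27%.

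**8. Table 5.** 0.80² = 0.64, 0.80³ = 0.51, 0.80⁴ = 0.41 and 0.80⁵ = 0.33. Rows 2 to 5 are successive powers of 0.80.

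**The case against.** **Completing the study is not the same as contributing to the endpoint.** The study lasts 18 months, but the primary window closes at month 15. Under {20c}, a patient with at least 80% of the window (to month 9 + 0.8 × 6 = 13.8) has only the remainder imputed. The article gives no dropout timing. Suppose the 27% falls evenly over 18 months (an assumption). The loss by month 15 is then 27 × 15/18 = 22.5%, leaving 70.5 per arm and 79.2% power. By month 13.8 it is 20.7%, leaving 72.2 per arm and about 80%. Earlier dropout moves the figure back towards 77%. This stands as a reason to tie the 77% to completers. It does not support the text as written, which makes no such argument and quotes study completers next to the 80%.

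**The main analysis keeps all 91 per arm.** This is true, but it does not yield 80%. Ninety-one fully observed patients per arm would give 88.4%. Patients with less than 80% of the window are imputed from months 0 to 3, when the article expects the arms to have similarly few ovulations. As an illustration, assume all 27% are imputed this way, with no difference between arms and an unchanged SD. The difference shrinks to 0.73 × 0.922 and power to about 63%. If half the effect survives in those patients, power is about 78%. The imputed analysis can therefore fall on either side of 77%.

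**The gap is small beside the uncertainty in the SD.** The pilot studies had 62 patients in total. If the SD rests on about 60 degrees of freedom (an assumption), its 95% interval is about 1.66 to 2.39, and power at 66.5 per arm runs from about 89% down to 60%. This limits the importance of the point but does not make the stated figure correct.

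**Conclusion.** The stated 80% does not follow from the stated inputs. If only the 66 or 67 completers per arm are counted, power for 0.922 is about 77%, and 80% power applies to a difference of about 0.96. The shortfall is about 3 percentage points at the first step. Severity is minor to moderate: no test, alpha level or patient number has to change.

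A reader might infer three stronger things that the documents do not support.

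- *That the planned analysis has exactly 77% power.* That is the completer calculation. Power under the intention-to-treat analysis depends on dropout timing and on the imputed values, and the article fixes neither.
- *That dropout was certainly added by multiplying.* The arithmetic fits, but no inflation formula is stated. The shortfall stands without this explanation.
- *That rows 2 to 5 of Table 5 become 59%, 45%, 35% and 27%.* These are powers of 0.77, and multiplication treats the tests as independent. Comparisons 1 to 3 share the placebo arm, and 1, 4 and 5 share SPIOMET. Using 0.922 at every step also does not describe one set of arm means: if PIO exceeds placebo by 0.922 and SPIOMET exceeds PIO by 0.922, SPIOMET exceeds placebo by 1.844. Those rows need recomputing, but not by this route.

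**What to change.** Keep N = 364. In Sample size {14} and row 1 of Table 5, use one of two statements:

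- about 77% power for a difference of 0.922 (80% power for about 0.96), counting only the 66 or 67 completers per arm expected at 27% dropout; or
- 80% power for a difference of 0.922, provided that no more than about 21% of patients are lost to the primary endpoint.

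State how dropout entered the calculation. If the sponsor relies on some dropout falling after the primary window, that assumption should be written down.

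Recompute rows 2 to 5 of Table 5 jointly, for example by simulating the fixed sequence with shared arms and a stated mean for each arm.

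The cost is a few sentences, one table and a short simulation. The stated power becomes slightly less favourable. No extra patients are needed. Holding both 80% and 27% dropout would instead take 99 per arm, 396 in total, which is 32 more than planned.

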**Sample size**		
**Total**	**364**	
Placebo	91	
PIO	91	
SPIO	91	
SPIOMET	91	
	**Minimal detectable mean differences** ^a^ ** and common standard deviations**	**Power** ^b^
1. Placebo vs SPIOMET	0.922 (1.96)	80%
2. Placebo vs SPIO	0.922 (1.96)	64%
3. Placebo vs PIO	0.922 (1.96)	51%
4. PIO vs SPIOMET	0.922 (1.96)	41%
5. SPIO vs SPIOMET	0.922 (1.96)	33%

^a^For ovulation rates

^b^Power to detect statistically significant differences within a fixed-sequence multiple testing approach

### Recruitment {15}

A total of 364 AYAs with PCOS will be recruited at the Outpatient Clinic of 7 hospitals from 4 European member states and 2 associated countries; the geographic distribution of the sites ensures ethnic variation.

The number of patients expected to be recruited are respectively:
*N* = 70 at HSJD – FSJD (Spain)
*N* = 46 at Hospital de Girona [name] – IDIBGI (Spain)
*N* = 54 at Azienda Ospedaliero-Universitaria S. Orsola, di Bologna (UNIBO) (Italy)
*N* = 39 at Odense University Hospital—UNIODE (Denmark)
*N* = 41 at St. Olavs Hospital – NTNU (Norway)
*N* = 72 at Medical University of Graz (Austria)
*N* = 42 at Istanbul Faculty of Medicine Topkapi – ISTA (Turkey)

## Assignment of interventions: allocation

### Sequence generation {16a}

Participant girls and young women will be randomly assigned in a 1:1:1:1 ratio to one of the following treatment groups: placebo, PIO, SPIO or SPIOMET. Treatment allocation will be done using Pocock-Simon Minimization Algorithm. Minimisation method ensures balance of treatments among the stratification factors. With this method, girls and young women will be dynamically allocated to one of the treatment arms with the lowest occurrence at the moment of randomisation with a probability of *p* = 0.9. The stratification factors will be clinical site, gynaecological age and BMI.

Medication kits will be packed in boxes with 12 kits per box. For this purpose, kit numbers and treatment arms will be randomly assigned in 12 blocks using PROC PLAN procedure, SAS 9.4.

The randomisation process ensures that all participants and all investigators performing the clinical visits and the assessments will be blinded for the allocated treatment.

### Concealment mechanism {16b}

Treatment allocation will be done via Interactive Web Randomisation System (IWRS) accessible through the electronic Case Report Form (eCRF) and randomisation codes will be generated. Once a patient is randomised to a planned treatment group, medication kits will be delivered according to the allocated treatment at time 0, 3, 6 and 9 months. Therefore, up to 4 medication kits will be assigned per subject. Each medication kit will contain enough medication for 3 months (3 bottles per kit; each bottle containing 35 pills).

### Implementation {16c}

When a patient meets all eligibility criteria, she will be randomised by the principal investigator at each recruiting centre via IWRS, and a randomisation code will be generated. Subsequently, the hospital pharmacy will receive the necessary information for delivering the allocated medication.

## Assignment of interventions: blinding

### Who will be blinded {17a}

The trial is designed as a double-blind study. Participating girls and young women will receive a daily tablet which will be indistinguishable among study groups. The tablets (all with exactly the same size and appearance) will contain placebo or the active compounds (PIO, SPIO or SPIOMET) depending on the study arm to which the patient will be allocated. Study participants, sites and study team members will remain blinded to the treatment allocation. The study blinding will be maintained throughout the clinical trial until data entry and processing are completed and the database has been locked.

### Procedure for unblinding if needed {17b}

In the event of a suspicion of an unexpected serious adverse reaction, the unblinding of the allocation of an individual participant will be requested for regulatory purposes. However, if possible and appropriate, the blinding will be maintained for the investigators and for those who will analyse and interpret the results at the study’s conclusion. The Sponsor will be notified before the blind is broken unless unblinding is required for a medical emergency necessitating knowledge of the blinded medication in the immediate management of the participant’s condition. In the latter case, the investigator will request the unblinding through the IWRS. The timing and rationale for the unblinding must be recorded in the source documentation.

## Data collection and management

### Plans for collection and assessment of outcomes {18a}

#### Collection of outcomes

Screening evaluation (time − 1).Study candidates will be recruited at the outpatient clinic of participating hospitals and written informed consent will be obtained. Medical history will be taken, including gynaecological age, menstrual regularity, clinically significant events over the past 5 years and the use of medication related to the PCOS phenotype and/or to the inclusion/exclusion criteria.Confirmation of eligibility will require a clinical visit (hirsutism and acne scores; BMI) and blood sampling [to assess blood count, electrolyte panel, lipids, glucose, insulin, ALT, AST, GGT, creatinine, urea, vitamin B12, folic acid, progesterone, 17-OH-progesterone, thyroid-stimulating hormone (TSH), androgens (testosterone, SHBG, FAI, dehydroepiandrosterone-sulphate), prolactin, ultra-sensitive human chorionic gonadotropin (us-HCG)]. Androgens will be measured in the early follicular phase of the cycle (days 3 to 7) or after 2 months of amenorrhea.

Baseline (time 0), on-treatment (3, 6, 9 and 12 months) and post-treatment (15 and 18 months) evaluations.Saliva samples for ovulation assessment (by progesterone measurement) will be collected weekly between 0 and 3 months (for 12 consecutive weeks during months 1, 2 and 3), between 9 and 12 months (for 12 weeks during months 10, 11 and 12) and between 12 and 15 months (for 12 weeks during months 13, 14 and 15).Clinical features will be collected at each time point (height and weight to infer BMI; waist and hip circumference to infer WHR; SBP and DBP; hirsutism and acne scores; menstrual regularity) besides information on concomitant medication and adverse events.At time 0, 6, 12 and 18 months, blood sampling will be performed in the fasting state to assess endocrine-metabolic, epigenetic and laboratory safety variables. At time 0, 12 and 18 months, additional blood sampling will be performed after 2 h of glucose upload for insulin and glycaemia assessment. At time 3, 9 and 15 months, blood sampling (for fasting insulin and glycaemia assessment) will be performed only in the event of clinically relevant hyperglycaemia observed at any time in the prior months.At time 0, 12 and 18 months, ultrasound, DXA and MRI will be performed for assessments of respectively cIMT, body composition, and partitioning of abdominal fat, including hepatic fat.Adherence to treatment will be assessed at each time point from baseline to time 12 months; whereas acceptability of the tablet will only be recorded at time 3 and 12 months.A highly sensitive serum or standard sensitive urine pregnancy test will be performed at each time point from baseline to time 12 months.At each time point from baseline to time 12 months, will attend to a LIP session, and fill in LIP-related questionnaires.At time 0, 6, 12 and 18 months, PROMs on HRQoL will also be assessed.Between hospital visits throughout the 18 months of study, the participants will record—in a diary—their menses, the time of any medication intake and any adverse event. Participants will deliver this diary at the next visit.At time 0 and 18 months, an online survey will collect information on the patient’s experience, respectively, during the enrolment process and throughout the 18 months of the actual study.

##### Saliva sampling

Saliva samples will be collected once weekly, on the same weekday, in the morning and in the fasting state, for 12 consecutive weeks during two timespans on-treatment (0–3 and 9–12 months) and one timespan post-treatment (12–15 months), yielding a total of 36 samples per study participant. The collection of saliva will be performed by spitting in a plastic container that will then be placed in a home freezer space (at − 20 °C), bearing a code number and also the date and time of sample collection. Samples will be kept frozen at home until transportation to the clinical centre, where samples will be processed and stored at fridge or freezing temperature. Once or twice yearly, samples will be shipped to HSJD where salivary progesterone concentrations will be measured.

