### Outcomes {12}

#### Primary outcome

The primary outcome will be the number of ovulations on-treatment and post-treatment (ovulatory function) by salivary progesterone analysis for 12 consecutive weeks during two periods on-treatment (months 0–3, and months 9–12), and during one period post-treatment (months 12–15). Information from salivary progesterone and from menstrual calendars (recorded in the patient’s diary) kept by the patients will be combined to infer each ovulation.

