##### Blood sampling

20 mL of peripheral blood will be sampled from each patient at times 0, 6, 12 and 18 months. During the OGTT at times 0, 12 and 18 months, an additional amount of 10 mL will be drawn 120 min after the glucose load. Collected blood samples will be stored at − 80 °C until shipment to UNIBO and HSJD for analysis (see below).

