#### Assessment of outcomes

##### Ovulatory function

Salivary progesterone will be centrally analysed at HSJD using an Enzyme-Linked Immunosorbent Assay (ELISA) [IBL-TECAN, Hamburg, Germany; intra- and inter-assay coefficients of variation (CVs) of 4.9 and 6.7%, respectively; salivary progesterone in the luteal phase, range: 87–550 pg/mL].

Saliva samples are a non-invasive, feasible method for monitoring progesterone levels across the menstrual cycle as they can be self-collected at home and stored in a home freezer for months before analysis [93]. Salivary progesterone concentrations are closely related to unbound serum progesterone [94]. This method has been previously used to assess ovulation rate in adolescents with type 1 diabetes and polycystic ovarian morphology [95, 96]; in one pilot study performed in HSJD, serum progesterone assessed by immuno-chemiluminescence, and salivary progesterone measured by the proposed method were highly correlated (*r* = 0.84; *p* < 0.0001; unpublished results). Two pilot studies performed in adolescent girls with PCOS have confirmed the reliability of salivary progesterone measurements [14, 15].

Information from salivary progesterone measurements and from menstrual diaries will be combined to infer ovulations and annualised ovulation rates. In the two previous pilot studies performed at HSJD [14, 15], with a similar ELISA method no longer available (Novatec, Immundiagnostica, Dietzenbach, Germany; intra- and inter-assay CVs < 10%), candidate ovulations were identified using a lower salivary progesterone cut-off of 99 pg/mL, as recommended by the manufacturer. All the ovulations that were confirmed by the above-mentioned two-step process were associated with salivary progesterone concentrations > 150 pg/mL. The progesterone cut-off derived from the ELISA assay to be used in the present study will be updated/rewritten when the new assay/method has been tested/validated. Candidate ovulations will be confirmed if the menstrual calendar mentions that menses did occur at least 2 weeks before and at most 2 weeks after obtaining the concerned saliva sample.

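### Sites may keep primary-endpoint saliva in a fridge, with no time limit, until a once- or twice-yearly shipment, although the protocol supports only frozen storage

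*Protocol article*

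**What the plan says.** The Primary outcome section makes saliva the biochemical basis of the trial's main result: "The primary outcome will be the number of ovulations on-treatment and post-treatment (ovulatory function) by salivary progesterone analysis". Menstrual calendars are then used to confirm each candidate ovulation.

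The Saliva sampling section describes weekly home collection into a freezer at −20 °C. "Samples will be kept frozen at home until transportation to the clinical centre", and the text continues with the storage rule at the centre and the holding time: "where samples will be processed and stored at fridge or freezing temperature. Once or twice yearly, samples will be shipped to HSJD", the central laboratory where progesterone is measured. The section gives no maximum fridge time, no fridge temperature and no rule for choosing between fridge and freezer.

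The Ovulatory function section justifies the method by saying of saliva samples that "they can be self-collected at home and stored in a home freezer for months before analysis". It reports no stability under refrigeration.

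The Blood sampling section sets one condition: "Collected blood samples will be stored at − 80 °C until shipment to UNIBO and HSJD for analysis".

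**The concern.** A centre that put saliva in a fridge on arrival and left it there until the next shipment would be following the article as written. With shipments once or twice a year, that could mean up to about 6 to 12 months. The article's own rationale covers months in a freezer, not months in a fridge. The specimen behind the primary endpoint therefore has a looser storage rule than the blood, which serves eligibility, secondary and safety variables.

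This matters because of how an ovulation is counted. A progesterone value must first exceed a cut-off, and only then is it checked against the menstrual calendar. A value that has become falsely low never becomes a candidate, and the diary cannot restore it. A loss of this kind is roughly proportional to the number of true ovulations, so it takes more from an arm with more ovulations and pulls the difference towards zero. If some of the seven sites refrigerate and others freeze, it also adds variation between sites. It cannot be repaired at analysis once the samples have changed.

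**Working it through.** **Step 1. What the text permits.**

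| Stage | Saliva (primary endpoint) | Blood |
|---|---|---|
| Home | Frozen, −20 °C | Not applicable |
| Centre, until shipment | Fridge or freezer, no time limit | −80 °C |
| Shipment to central laboratory | Once or twice yearly | Interval not stated |
| Storage support given | Home freezer, for months | Not needed for this point |

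Long refrigeration is permitted, and the article offers no support for it.

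**Step 2. How far a value would have to fall.** The only relevant figures come from the pilot studies' assay (Ovulatory function). The cut-off for a candidate ovulation was 99 pg/mL, and all confirmed ovulations were above 150 pg/mL. A value at 150 would be missed only after a fall of more than 1 − 99/150 = 34%. That assay is no longer available. The cut-off for the trial assay is to be set after validation, so the margin in this trial is unknown. The trial assay's stated luteal range starts at 87 pg/mL.

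**Step 3. Illustration of impact.** The documents give no rate of loss. Let f be the assumed overall share of true ovulations missed, equal in all arms.

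Inputs from Sample size {14}: difference 0.922, SD 1.96, two-sided 5%, two-sample *t*-test. By the *t*-test, 72 per arm is the smallest size giving 80% power (80.0%), and it serves as the reference.

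Diluted difference = 0.922 × (1 − f):
- f = 5%: 0.922 × 0.95 = 0.876
- f = 10%: 0.922 × 0.90 = 0.830
- f = 20%: 0.922 × 0.80 = 0.738

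For the SD, two cases are shown:
- (a) SD held at 1.96.
- (b) SD reduced because counts are thinned: SD′ = √[(1 − f)² × 1.96² + f(1 − f) × μ], with the mean count μ assumed to be 1 to 3. For example, with f = 20% and μ = 2: √(0.64 × 3.8416 + 0.16 × 2) = √2.779 = 1.667.

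| f | Difference | Power, n = 72, (a) | Power, n = 72, (b) | Power, n = 91, (a) | Power, n = 91, (b) |
|---|---|---|---|---|---|
| 0 | 0.922 | 80.0% | 80.0% | 88.4% | 88.4% |
| 5% | 0.876 | 75.9% | 78–80% | 85.0% | 87–88% |
| 10% | 0.830 | 71.3% | 77–79% | 81.1% | 86–88% |
| 20% | 0.738 | 61.1% | 73–78% | 71.4% | 82–86% |

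The columns for 91 per arm treat every randomised patient as fully informative. That is optimistic, because patients who drop out have imputed values.

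If only a share s of patients has refrigerated samples and a fraction g of their ovulations is lost, then f = s × g. Half the patients with a 20% loss gives f = 0.5 × 0.2 = 10%.

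**The case against.** The strongest reply is that the harm is not shown. The documents do not say that progesterone falls in refrigerated saliva, at what rate, or that any fall grows with time. This stands: degradation and its size are assumptions here.

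A second reply is that the fridge may be meant only for the hours around processing, and that a laboratory manual, not shown, may set the temperature. Both may be true. Sites have freezers for blood, so months in a fridge may never occur. But the article is not merely silent on this. It states a permissive rule, and the sentence after it sets an interval of months. If a manual is stricter, the two texts should agree.

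Third, the power loss is easily overstated. The fall to 61% needs a 20% overall loss and an SD that stays at 1.96 while counts shrink. If the SD shrinks too, power is about 73–78% at the same loss. The pilot margin of 34% also suggests that modest losses could leave many ovulations above the cut-off. Both points stand, except that the pilot margin cannot be carried over to an assay whose cut-off is not yet set.

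A reader might also infer that spoiled samples could produce a false benefit for an active arm. The documents do not support that. Treatment is blinded, site is a minimisation factor, and the primary analysis takes the stratification factors into account. Any loss should therefore affect arms alike within a site.

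**Conclusion.** The point holds as a defect in a stated storage rule. The article permits fridge storage of unlimited duration for the specimen on which the primary endpoint depends, and it supports only frozen storage.

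The possible consequence is attenuation and between-site noise. Under an assumed overall loss of 5% to 20% of ovulations, the planned difference would shrink from 0.922 to between 0.88 and 0.74. With 72 per arm, power would fall from 80% to between 76% and 61% if the SD is unchanged, or to between about 80% and 73% if it shrinks with the counts. These figures rest on an assumed loss, equal across arms, and on an assumed mean count of 1 to 3 for the shrinking SD. They are not a forecast. The documents do not show that refrigerated samples will degrade, and they give no ground to expect a bias in favour of any arm.

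This should be fixed, because the change is cheap and samples that have changed cannot be recovered. Confidence is moderate: the text is clear, but the size of the effect is unknown.

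**What to change.** In Saliva sampling, remove the option of fridge storage at the centre. State that saliva is kept frozen at −20 °C or colder from receipt until assay, shipped frozen, and thawed only for processing. If some refrigeration is unavoidable, state instead a maximum fridge time supported by stability data from the trial assay. Align any laboratory manual with the same wording.

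Record storage condition and duration for each sample, including samples already collected. Plan a sensitivity analysis that treats a 12-week period with affected samples as missing. Single weekly samples should not simply be deleted: an ovulation can be seen only in the samples that remain, so deletion would itself lower the count or bring in the article's imputation rule for incomplete assessment.

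The cost is one or two sentences, a storage field per sample, and freezer space for up to 36 saliva samples per participant at sites that already store blood at −80 °C.
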